## Abstract

**Background:**

Alzheimer’s disease, a global public health issue, accounts for 60 to 80% of all dementias. Alzheimer’s disease primarily causes cognitive impairment and drugs have only modest short-term effects, highlighting a pressing need to develop effective interventions. Aerobic exercise holds promise for treating cognitive impairment in Alzheimer’s disease through biologically sound mechanisms. Nonetheless, aerobic exercise studies in Alzheimer’s disease are limited with mixed findings.

**Methods/Design:**

This pilot randomized controlled trial will investigate the effects of a 6-month, individualized, moderate-intensity cycling intervention (20 to 50 minutes per session, 3 times a week) on cognition and hippocampal volume in community-dwelling older adults with mild-to-moderate Alzheimer’s disease. The specific aims are to: 1) determine the immediate effect of the cycling intervention on cognition in Alzheimer’s disease; 2) examine if the cycling intervention slows cognitive decline in Alzheimer’s disease from baseline to 12 months; and 3) assess the effect of aerobic exercise on hippocampal volume over 12 months. Ninety subjects will be randomized on a 2:1 allocation ratio to cycling or attention control (low-intensity stretching) and followed for another 6 months. Allocations will be concealed to all investigators and outcome assessors will be blinded to group assignments and previous data. Cognition will be measured by the Alzheimer’s disease Assessment Scale-Cognition at baseline before randomization and at 3, 6, 9, and 12 months. Hippocampal volume will be measured by magnetic resonance imaging at baseline and 6 and 12 months. The sample size of 90 will give 80% power to detect a 2.5-point difference in within-group changes in the Alzheimer’s disease Assessment Scale-Cognition at 6 months for the cycling group.

**Discussion:**

Findings from this study will address the critical gap of exercise efficacy in Alzheimer’s disease and use of magnetic resonance imaging as an outcome measure in clinical trials. This study will provide a potential treatment that may increase physical function and quality of life and curb the prohibitive costs for the growing dementia population.

**Trial registration:**

Primary registration: (NCT01954550; date of registration: 20 September 2013). Secondary registration: (NCT01954550; date of registration: 1 October 2013).

**Electronic supplementary material:**

The online version of this article (doi:10.1186/1745-6215-15-394) contains supplementary material, which is available to authorized users.

## Background

Dementia is a global public health issue, affecting 35.6 million people and costing $604 billion worldwide in 2010. Alzheimer’s disease (AD) is the most common type of dementia and accounts for 60 to 80% of all dementias [1]. The hallmark symptoms of AD are cognitive impairment (in at least two cognitive domains) and functional decline, which can lead to behavioral and psychological symptoms of dementia (BPSD), loss of independence, poor quality of life, and premature institutionalization [2, 3]. In addition, available drugs have only modest short-term effects on reducing cognitive impairment in AD [4]. Hence, there is a pressing need to develop non-pharmacological interventions for alleviating AD symptoms. To this end, aerobic exercise is promising due to its ability to increase gray-matter volumes in the hippocampus, improve cerebral blood flow, neuroplasticity and neurogenesis, increase production and function of neurotransmitters and neurotrophic growth factors, and reduce AD pathologic β-amyloid load [5–7].

### Effect of aerobic exercise on cognition

At least five meta-analyses of randomized controlled trials (RCTs) have been conducted demonstrating that aerobic exercise produced mild-to-moderate cognitive gains in adults without AD and dementias [8–12]. Similar cognitive improvements were found from aerobic exercise in persons with mild cognitive impairment (MCI) and dementia [13–16]. One meta-analysis even showed that aerobic exercise improved memory to a greater degree in persons with MCI (Hedges’ g = 0.237, *P* = .05) than in those without MCI (g = 0.096, *P* = .143) [12]. Together, these findings lend preliminary support to that aerobic exercise provides a therapeutic effect on cognition in AD, which is demonstrated by emerging aerobic exercise studies in AD. Cycling or walking for 5 to 12 weeks improved scores on the Mini-Mental State Examination (MMSE) from 16.3 at baseline to 19.8 post training (*P* < .001, n = 35) [17]. In another study, 15 men with AD increased scores on the Test of Attention Matrix from 35.9 to 43.0 and the MMSE from 19.4 to 21.7 from baseline to 3 months (all *P* < .001) after completing a 3-month moderate-intensity cycling intervention [18]. However, these studies did not have a control group.

Other researchers have found that aerobic exercise did not necessarily result in dramatic cognitive gains, but was potentially involved in stemming the progression of cognitive decline in AD. For instance, relative stability in cognitive status, as measured by the AD Assessment Scale-Cognition (ADAS-Cog), was observed in a sample of 11 [19] and 26 [20]) subjects who underwent moderate-intensity cycling for 6 months.

Furthermore, multicomponent interventions with aerobic exercise as a component showed differing effects. One study reported improved cognition as measured by the French Rapid Evaluation of Cognitive Function scale (n = 38) [21], but other studies demonstrated no changes on the Boston Naming Test (n = 27) [22] or the Hopkins Verbal Learning Test (n = 11) [23].

Together, the above findings indicate that aerobic exercise could either maintain or improve cognition in persons with AD, which are very positive findings given that progressively worsening cognition marks the course of AD. Nonetheless, aerobic exercise studies in AD are few and have been limited by such factors as small sample sizes, variable comparator groups, inconsistent cognitive measures, variable domains of cognition as a main outcome, and application of multicomponent interventions that masked the true effect of aerobic exercise [24]. The comparability of those findings is further limited due to the varied doses of aerobic exercise [24]. The doses rarely met the weekly 150-minute moderate-intensity level of exertion that has been recommended for older adults or the 6-month duration considered sufficient for producing cognitive gains in non-AD samples [7]. The prescribed exercise frequency ranged from 1 to 5 times a week, session duration from 20 to 40 minutes, intensity from very low to moderate, and program duration from 5 weeks to 4 years across the studies [17–21, 23, 25–31]. In addition, there was substantial discrepancy between prescribed and delivered exercise doses. Methods for ensuring exercise delivery are often unreported, while the retention and adherence rates ranged from 59 to 92% and 10 to 90%, respectively [19–22, 25, 27–31]. It is likely that a dose–response relationship between exercise and cognition exists, but remains unknown due to unclear exercise adherence and treatment fidelity.

### Effect of aerobic exercise on hippocampal volume

AD neuropathology includes β-amyloid plaques and neurofibrillary tangles that cause neurodegeneration and brain atrophy that begins and is most severe in the medial temporal lobe, particularly in the hippocampus [32]. To measure those changes *in vivo*, magnetic resonance imaging (MRI) has been developed and validated as a tool for segmenting and calculating whole and regional brain volumes, indicating an annual 3 to 5% decline in hippocampal volume in AD [33–35]. While MRI has been studied for diagnosing AD and predicting the progression from mild cognitive impairment to AD, its use as an outcome measure in RCTs is just emerging [36–41]. Although no aerobic exercise studies in AD have used MRI, aerobic exercise has been found to increase hippocampal volume in nondemented individuals [42–44].

In summary, the current evidence supports the hypothesis that aerobic exercise might reduce cognitive decline in AD and limit the progression of AD neuropathology. However, previous studies often did not use a control group and lack a rigorously designed and delivered aerobic exercise intervention. Even if aerobic exercise shows no direct benefits to AD’s symptoms and progression, persons with AD will nevertheless receive the same health benefits from aerobic exercise, such as improved physical function, as any other populations.

### Study aims

The objective of this paper is to report the study protocol of a pilot RCT that investigates the effects of a 6-month, individualized, moderate-intensity cycling intervention on cognition and hippocampal volume in AD by piloting all components of a future full-scale RCT. The study is funded by the National Institutes of Health’s National Institute on Aging (1R01AG043392-01A1, 1 August 2013 to 30 April 2018). The specific aims and hypotheses of the study are:

#### Aim I: determine the immediate effect of the cycling intervention on cognition in AD

##### Hypothesis 1a

Intervention subjects will have a smaller within-group increase in ADAS-Cog at 6 months than placebo subjects in AD drug RCTs.

##### Hypothesis 1b

Control subjects will have the same within-group increase in ADAS-Cog at 6 months as placebo subjects in AD drug RCTs.

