### Sample size

The primary endpoint is the 6-month within-group change in the ADAS-Cog, compared with the mean increase of 3.2 points from pooled placebo groups in AD drug RCTs with a total sample size of 534 (assuming equal numbers of mild and moderate AD subjects) [48]. Power calculations were based on a one-sample *t-* test (2-sided) at the 0.05 level, using the pooled standard deviation (SD) = 6.25 from the same placebo groups in AD drug RCTs [48]. Sample size was further determined by factoring in 16% attrition, which was based on the attrition rates from our previous studies [19, 20], 12 to 41% attritions in AD drug RCTs [49], and 0 to 41% attritions in non-AD exercise RCTs [12]. As a result, we will enroll 90 subjects and randomize 60 to the cycling group and 30 to the control group. The power calculation is conservative as it does not account for the stratified randomized design (or equivalently assumes that there is no difference between the strata, see below).

If 50 subjects in the exercise group complete the 6-month measurement, then the study has 80% power to detect a difference of at least 2.5 points with a one-sample 2-sided *t*-test at the 0.05 level. That is, if cycling leads to a true mean increase in the ADAS-Cog of no more than 0.7 points, the study will have 80% power to detect a difference from the increase of 3.2 observed in placebo groups in AD drug RCTs. In our control group, if 25 complete the trial, then the expected half-width of the 95% confidence interval for the mean 6-month change in the control group is 2.4. Although there is little power to detect a difference between our controls and the placebo groups in AD drug RCTs, our trial will provide a valuable estimate of the intervention’s Hawthorne effect.

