#### Aim 1: determine the immediate effect of the cycling intervention on cognition in Alzheimer’s disease

The primary comparison for both hypotheses in Aim I will be a 2-sided test of the overall mean in a 1-way ANOVA with age stratum as the factor and the change in ADAS-Cog from baseline to 6 months as the response against the null hypothesis value of 3.2 points, which is the mean 6-month increase in ADAS-Cog in pooled placebo groups of AD drug RCTs (n = 534) [48]. Separate ANOVAs will be run for each randomization group. Because we stratified treatment assignment (by age) in the design of the study, it is important that we account for this in the analysis of the trial data in order to realize the improved power of this design. Missing values at 6 months will not be imputed by last-observation-carried-forward because this would bias the mean change toward zero. Further analysis will use an analysis of covariance (ANCOVA) to determine significant difference in ADAS-Cog between groups at 6 months after adjusting for other covariates, including baseline ADAS-Cog and age stratum as covariates. Other covariates and potential outcome variables at baseline (Table 4) will be screened for possible inclusion in the model if any are associated with ADAS-Cog at a *P* < .1 level.

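### Hypothesis 1b says controls will match drug-trial placebo, but its primary comparison is a difference test in about 25 controls, which cannot support that claim

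*Protocol article*

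**What the plan says.** Under Study aims, Hypothesis 1b reads: "Control subjects will have the same within-group increase in ADAS-Cog at 6 months as placebo subjects in AD drug RCTs". This is a claim of sameness.

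The Statistical analyses section for Aim 1 fixes how it is tested: "The primary comparison for both hypotheses in Aim I will be a 2-sided test of the overall mean in a 1-way ANOVA". The response is the 6-month ADAS-Cog change, the model includes the age strata, and the mean is tested "against the null hypothesis value of 3.2 points". It adds: "Separate ANOVAs will be run for each randomization group". Controls are thus tested alone against 3.2, exactly as the cycling arm is. No equivalence margin or interval criterion is attached to 1b.

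The Sample size section gives the planning figures. The reference mean is 3.2 points, and the calculations were made "using the pooled standard deviation (SD) = 6.25 from the same placebo groups in AD drug RCTs". If 25 controls complete, "the expected half-width of the 95% confidence interval for the mean 6-month change in the control group is 2.4". The section then concedes the limitation ("Although there is little power to detect a difference between our controls and the placebo groups in AD drug RCTs") and says that the control arm will still provide a useful estimate of the Hawthorne effect.

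**The concern.** The two Aim I hypotheses point in opposite directions. For 1a, rejecting 3.2 in the favourable direction supports the hypothesis. For 1b, the hypothesis is itself the null value, so rejection contradicts it and non-rejection leaves it unproven. Giving both the same primary comparison leaves 1b with a test that has no outcome able to confirm it.

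In a small arm this matters in practice, because non-rejection is likely whether or not controls behave like drug-trial placebo patients. Hypothesis 1b is the protocol's only stated check within Aim I that 3.2 suits this population. The Discussion explains that the hypotheses were built on a historical control because the between-group comparison lacked power. If an uninformative non-significant result were taken as confirming 1b, it would lend unearned credibility to the 3.2 benchmark and so to the result for 1a.

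**Working it through.** **Inputs, all from the protocol article**
- Reference value: 3.2 points (Sample size; Aim 1 analysis).
- SD of the 6-month change: 6.25 (Sample size).
- Test: one-sample t-test, two-sided, alpha 0.05 (Sample size).
- Completers: 25 controls and 50 cyclists (Sample size). These agree with 16% attrition: 30 × 0.84 = 25.2 and 60 × 0.84 = 50.4.
- True departure of controls from 3.2: not given. It is assumed below and shown over a range.

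**Step 1: reproduce the plan's own figures**

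Standard error of the control mean = 6.25 / √25 = 1.25.

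| Quantile | Half-width of 95% interval |
|---|---|
| Normal, 1.95996 | 1.95996 × 1.25 = 2.44995, which rounds to the stated 2.4 |
| t, 24 df, 2.0639 | 2.0639 × 1.25 = 2.58 |
| t, 22 df (three age strata), 2.0739 | 2.0739 × 1.25 = 2.59 |

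The stated 2.4 is therefore the normal-quantile value. The companion statement for cycling (50 completers, 2.5 points, 80% power) also holds: 0.792 by the noncentral t and 0.807 by the normal approximation.

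**Step 2: how often the control test is non-significant**

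Noncentrality = departure / 1.25. The test rejects when |t| exceeds 2.064 (24 df).

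| Assumed departure from 3.2 | Noncentrality | Power | Non-significant |
|---|---|---|---|
| 1.0 | 0.8 | 0.120 | 88% |
| 1.5 | 1.2 | 0.211 | 79% |
| 2.0 | 1.6 | 0.336 | 66% |
| 2.5 | 2.0 | 0.484 | 52% |
| 3.2 | 2.56 | 0.690 | 31% |

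With no departure at all, the test is non-significant 95% of the time by construction. Going from a true departure of 0 to one of 1.0 therefore moves that probability only from 95% to 88%. Using 22 df for the age strata changes the power by at most 0.003 (for example 0.481 instead of 0.484 at 2.5 points). A departure of about 3.65 points is needed for 80% power.

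**Step 3: could 1b be kept as a formal equivalence claim?**

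The margin is an assumption, because the document gives none. Two one-sided 5% tests, true difference zero, SD 6.25:

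| Assumed margin | Power with 25 controls | Completers for 80% power (normal approximation) |
|---|---|---|
| 2.0 | 0.05 | 84 |
| 2.5 | 0.24 | 54 |
| 3.0 | 0.51 | 38 |
| 3.2 | 0.60 | 33 |

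Even a margin as wide as the whole reference change of 3.2 needs more completers than the 30 controls to be randomized. This design can estimate the control change, but it cannot show sameness with adequate power.

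**The case against.** The strongest defence is that the protocol already treats the control arm as a source of an estimate. The Sample size section gives an expected confidence interval, admits low power against the historical value and names estimation of the Hawthorne effect as the benefit. Nowhere does it say that a non-significant result will be taken as support for 1b; that reading follows from pairing this hypothesis with this test. A reader would also not be left with the two one-sample results alone. The Aim 1 analysis includes a 6-month ANCOVA between groups adjusted for baseline ADAS-Cog and age stratum, mixed models with a group-by-time interaction follow, and Hypothesis 2 is itself between-group. This is, moreover, a self-described pilot. All of that stands and limits the seriousness of the point. It does not remove it, because the Aim 1 analysis still names the difference test as the primary comparison for 1b and the hypothesis still asserts sameness.

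Three stronger readings are tempting, and the document does not support them.
- **That the half-width of 2.4 is wrong.** It reproduces from the stated SD and sample size with the normal quantile. A t-based value of about 2.6 would match the t-test named in the same section, but that is a choice of method and changes no conclusion.
- **That a misleading pattern (1a significant, 1b not) would often arise when cycling does nothing.** If both arms shift equally from 3.2, the pattern's frequency depends wholly on the assumed shift: about 5% at no shift (0.05 × 0.95), 30% at 1.5 (0.384 × 0.789), 40% at 2.0 (0.602 × 0.664) and 41% at 2.5 (0.792 × 0.516). The document gives no basis for choosing a shift, and the result says more about the historical comparator for 1a than about the test of 1b.
- **That the direct cycling-minus-control difference should become the primary comparison.** The Discussion considers this and declines it on stated power (50% at 3.5 points, 80% at 5 points). Replacing the primary comparison is a larger design question than the wording of 1b.

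**Conclusion.** The point holds in a narrow form. Hypothesis 1b is a claim of sameness whose primary comparison is a two-sided difference test with no margin, so its result can refute the claim but cannot support it. With 25 completing controls, an SD of 6.25 and a two-sided 0.05 level, the test would be non-significant about 88%, 79%, 66% or 52% of the time for true departures of 1.0, 1.5, 2.0 or 2.5 points. A control departure as large as the effect that the cycling arm is powered to detect would thus be missed about half the time. These departures are assumptions chosen to show the range; the SD, sample size and alpha are the protocol's own. The disclosed low power and the estimation purpose soften the problem. The wording should still be changed, because the present pairing invites an invalid inference and the correction is nearly free.

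**What to change.** - Restate Hypothesis 1b as an estimation objective: report the control group's mean 6-month ADAS-Cog change with its 95% confidence interval beside the reference value of 3.2.
- In the Aim 1 analysis, limit the primary test against 3.2 to Hypothesis 1a and remove it as the primary comparison for 1b.
- State that a non-significant difference from 3.2 in controls is not evidence that they match drug-trial placebo patients.
- State that the result for 1a will be read alongside the 6-month between-group ANCOVA that is already planned.
- Optional refinement: give the expected half-width as about 2.6, so that the interval uses the same t distribution as the named test, or note that 2.4 uses the normal quantile.

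The cost is a few sentences of protocol wording, with no extra participants or data. The one real loss is that 1b no longer has a yes/no test. A pre-specified equivalence margin would keep one, but with about 25 controls its power would be low for any margin up to 3.2 points.

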#### Aim II: examine if the cycling intervention slows cognitive decline in AD from baseline to 12 months

##### Hypothesis 2

Intervention subjects will show a smaller increase in ADAS-Cog over 12 months than control subjects.

#### Aim III: assess the effect of aerobic exercise on hippocampal volume in AD over 12 months using MRI

##### Hypothesis 3

Intervention subjects will have a smaller decrease in hippocampal volume over 12 months than control subjects.

## Methods

### Design

The planned design of this pilot RCT includes two parallel groups on a 2:1 (cycling:stretching) allocation ratio with allocation concealment and assessor blinding. The design adheres to the Standard Protocol Items Recommendations for Interventional Trials (SPIRIT) [45], the Consolidated Standards of Reporting Trials (CONSORT) elements [46], and the World Health Organization Trial Registration Data Set Version 1.2.1 guidelines (http://www.who.int/ictrp/network/trds/en/) for clinical trials protocols. Ninety community-dwelling older adults with mild-to-moderate AD will be enrolled: 60 will be randomized to the 6-month intervention (20 to 50-minute moderate-intensity cycling, 3 times a week) and 30 will be assigned to attention control (20 to 50-minute stretching exercise, 3 times a week; Figure 1). Cognition will be assessed at baseline before randomization and at 3, 6, 9, and 12 months, while hippocampal volume will be measured by MRI at baseline before randomization and 6 and 12 months. All data collectors will be blinded to the group assignments. This study is approved by the University of Minnesota’s Institutional Review Board (IRB: #1306M35661). Informed consent will be obtained from all participants. In the event that participants could not consent for themselves, they will give assent while their families or friends, in the descending order of power of attorney, spouse, adult children, and significant others will provide surrogate consent.

**Figure 1 Fig1:**
[figure not shown]
**Subject enrollment flow diagram.**

### Setting

Different aspects of the study activities will be conducted at different sites, including the university’s Clinical and Translational Science Institute (CTSI), Center for Magnetic Resonance Resources, School of Nursing Laboratory of Clinical Physiology, Aging and Dementia Imaging Research laboratory at Mayo Clinic, MN, Young Men’s Christian Association (YMCA) gymnasiums, and exercise rooms of retirement communities. Subject screening and data collections will occur at the CTSI. MRI scan will be conducted at the Center for Magnetic Resonance Resources, but MRI quality control and data processing will happen at the Aging and Dementia Imaging Research laboratory at Mayo Clinic. Exercise testing will be conducted at the Laboratory of Clinical Physiology. Cycling and stretching exercises will be delivered at YMCA gyms, exercise rooms of the retirement communities, or the Laboratory of Clinical Physiology, to minimize travel for the subjects. Study staff involved in exercise delivery will provide transportation for all enrolled subjects to attend all study activities using a rented university vehicle with liability coverage.

